# Effectiveness of an individualized program of muscular strength and endurance with aerobic training for improving germ cell cancer-related fatigue in men undergoing chemotherapy: EFICATEST study protocol for a randomized controlled trial

**DOI:** 10.1186/s13063-015-1143-x

**Published:** 2016-01-05

**Keywords:** Testicular cancer, Germ cell cancer, Physical exercise, Cancer-related fatigue, Chemotherapy, Clinical rules, Metabolomics

## Abstract

**Background:**

Patients with testicular germ cell cancer (GCC) have a high cure rate; however, cancer-related fatigue is the most common complication among patients with GCC undergoing treatment with chemotherapy. Although exercise is widely recommended, information about the physio-pathological effects of cancer therapy on skeletal muscle is very limited. Our aim is to evaluate the effects of an individualized program of muscular strength and endurance with aerobic training on cancer-related fatigue.

**Methods/Design:**

The present study is a randomized controlled trial comparing an individualized program of muscular strength and endurance with aerobic training compared to a control group. We will conduct this trial in patients undergoing chemotherapy, recruited by the Department of Oncology of Virgen de la Victoria Hospital (Málaga). Patients will be included and evaluated before the first cycle of chemotherapy and assigned randomly to the experimental or control group. Cancer-related fatigue, physical condition and biological samples will be measured at the beginning and at the end of an 8-week intervention by the same evaluator, who will be unaware of the allocation of participants to each group. Furthermore, there will be monitoring for 6 months (24 weeks) after training for all outcome variables.

**Discussion:**

This study hopes to offer patients with GCC an individualized exercise program with aerobic training for cancer-related fatigue. Such a scheme, if beneficial, could be implemented successfully within public health.

**Trial registration:**

ClinicalTrials.gov Identifier: NCT02433197. Date of registration: 13 April 2015.

## Background

Testicular germ cell cancer (GCC) represents 1 % of all human cancers and its incidence has increased by 1 % over the last 50 years [1, 2]. In young men, it represents one of the most malignant forms and is the second commonest cause of cancer-related death [1, 2]. Testicular tumor cell growth constitutes the majority of testicular malignancies [2]. GCC patients have a high cure rate, and are sensitive to radiation and chemotherapy, but 5 % of patients develop resistance to treatment.

Impaired muscle function and cancer-related fatigue (CRF) are two of the most common complications among patients in additiounder chemotherapy [3]. Moreover, early, localized muscular fatigue and severe deconditioning are common observations in clinical practice involving GCC patients undergoing chemotherapy [4]. The cause of this muscle deconditioning is unknown and although the effects of antineoplastic drugs have been described in some detail [4, 5], the way these effects may affect the phenomenon of CRF is poorly described. With growing interest in the duality oncology-physical exercise, many studies are now focused on the implementation of physical exercise as a complementary intervention to anti-cancer therapy [6]. Although exercise is widely recommended, information about the physio-pathological effects of cancer therapy on skeletal musculature is very limited [7]. Severe and chronic fatigue has been found in 30 % of long-term GCC survivors many years after the end of primary treatment [8]. The phenomenon known as “cancer-related fatigue” is characterized by being more severe, more distressing and having less chance of relief through rest than in the general population [9]. Although there are several questionnaires to assess CRF [10], a complementary method such as semi-structured [11] could be used.

Treatment with aerobic training in association with education has been shown to induce clinically very significant improvements in breast CRF [4]. In addition, a program of strength and muscular endurance training has been shown to attenuate the reductions in fiber size and strength in healthy subjects and patients [4, 12].

Metabolomics is an emerging discipline, defined as a multidisciplinary science that requires cooperation between chemists, biologists and computer scientists. Metabolome is the term used to refer to the complete inventory of small molecules, non-protein compounds, such metabolic intermediates, ATP, fatty acids, glucose, cholesterol, hormones, and other signaling molecules, and secondary metabolites found in a biological sample [13, 14]. As such, the metabolome changes continuously, depending on the activation and interaction of the various metabolic pathways inside the cell. It also reflects the phenotype that can be used to interfere gene function. Although genomics and proteomics can provide important information on expected function, metabolomics provides an immediate snapshot of all biological functions that reflect current events at a specific time [15].

The primary objective of the study is to investigate the short- and long-term (6 months) effects of an individualized program of muscular strength and endurance with aerobic training to improve CRF. A secondary goal is to examine the tolerance of muscular endurance training started on day 1 of the course of cancer treatment on muscle deterioration. Furthermore, the effect of the program on metabolomic level and on various fitness and quality-of-life parameters will be analyzed to try and establish rules of clinical prediction by multivariate regressions. The hypothesis of our study is that a program of muscular strength and endurance with aerobic training to improve CRF can be designed.

## Methods/Design

### Design and participants

The present study is a randomized controlled clinical trial conforming to Consolidated Standards of Reporting Trials (CONSORT) guidelines, comparing an individualized program of strength and muscular endurance with aerobic training versus a control group. All variables will be measured at the beginning and the end of the 8-week intervention by the same evaluator, who will be unaware of the allocation of participants to each group. Furthermore, there will be monitoring for 6 months (24 weeks) after training for all outcome variables. Evaluations will be completed in the Area Health Patronage of Sports, Torremolinos, Spain.

GCC patients between 18 and 45 years who are due to undergo chemotherapy at the University Hospital of Málaga will be included in the study. The sample selection will be among those with performance status (PS) ≤1. Patients will be included and evaluated before the first cycle of chemotherapy and assigned to the experimental or control group randomly by using hidden envelopes. Potential participants will be contacted by the study coordinator and all doubts will be resolved before giving their written consent from each participant. The expected flowchart is shown in Fig. 1. The study had ethics approval from the Comité de Ética de la Investigación Provincial de Málaga (Consejería de Salud Servicio Andaluz de Salud, Spain). The principles of the Declaration of Helsinki are respected.

**Fig. 1 Fig1:**
[figure not shown]
Flow chart of the study

### Treatment

Antineoplastic therapy for GCC will consist of cisplatin 20 mg/m^2^ and etoposide 100 g/m^2^ daily for 5 days and bleomycin 15,000 IU/m^2^ weekly. Three cycles of this combination will be administered in 3-week cycles.

### Intervention

The intervention will be an 8-week individualized program of muscular strength and endurance with aerobic training, led by physiotherapists in groups of eight to ten participants. The 8-week program is a good balance between the minimum necessary to produce physiological improvements and the maximum to avoid drop-out. Each program will be individualized based on the evaluations of muscular strength and endurance as well as determination of the aerobic-anaerobic zone transition described in previous studies [16–19]. Sessions will be of 1 hour duration, three times a week. Each session will consist of 30 minutes of strength exercises and 20 minutes of continuous exercises in the aerobic-anaerobic zone transition.

Land-based exercises to improve muscular strength and endurance will follow the protocol described by Andersen and Aagaard [12]. In weeks 1 and 2, participants carry out 3 sets of 15 repetitions (reps) to become familiar with the exercises. From week 3 onwards, participants will perform 4 sets of 10 reps. If the participant can do more than 12 reps, the weight to be lifted will be increased. All exercises are carried out under supervision to ensure proper technique and adequate progression.

Aerobic training exercises will be performed using a cycloergometer [16]. In weeks 1 and 2, participants perform a low-level intervallic adaptation to adapt to the experience of fatigue during exercise. For the six remaining weeks, participants will be instructed to maintain a constant rhythm in the cardiac training prescribed based on an individual test [16] and their gradual adaptation to lactate tolerance [6]. If the participant experiences discomfort or severe fatigue during intense exercise, intensity will be reduced whilst maintaining the objective whenever possible. Participants will be encouraged to participate in all sessions and will be continually reminded of the importance of adherence in order to achieve the objectives.

Both groups, intervention and control, receive a printed decalogue based on common psychosocial issues for GCC survivors: having cancer and its implications, stress, distress, uncertainty, fear and anxiety, doubts about body image, family relations and future prospects [20]. The control group will be instructed to continue their current activities and to not objectively increase levels of physical activity performed during the 8-week intervention.

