### Sample size

Version 3.1 G-Power was used to estimate the sample size and a minimum of 20 subjects per group (10 % loss) will be required “a priori” to have sufficient statistical power (80 %), alpha error (0.05) and a clinical effect Cohen’s *d* = 0.87 in the QuickPIPER scale of CRF [24].

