### Statistical treatment

For analysis of the results, a database will be created using the information collected from participants’ notebooks (questionnaires, interviews, physical tests and biological tests). Intention-to-treat analysis of all participants will be developed. After the intervention phase, descriptive statistics are performed with measures of central tendency and dispersion of the study variables. This is followed by inferential analysis by difference values between the outcome variables in both groups. In addition, multiple regression analysis of potential predictors is carried out to determine clinical prediction rules for severe fatigue and other effects of cancer treatment. The size of intergroup effect will be calculated (Cohen’s *d*). An effect size <0.2 reflects a negligible difference, between ≥0.2 and ≤0.5 a small difference, between ≥0.5 and ≤0.8 a moderate difference, and ≥0.8 a large difference. A value of *p* <0.05 will be considered statistically significant. SPSS V 21.0 will be used in Mac version for data analysis.

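### The sample size makes no allowance for group delivery of exercise in one arm; if outcomes correlate within exercise groups, power falls and an unadjusted comparison exceeds 5% error

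*Protocol article*

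**What the plan says.** All references are to the protocol article.

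- **Design and participants:** patients are randomised individually, before their first chemotherapy cycle, with concealed envelopes.
- **Intervention:** the exercise programme is "led by physiotherapists in groups of eight to ten participants", in supervised sessions three times a week for 8 weeks. Loads and cycling intensity are set from each patient's own tests. Controls carry on with their usual activities and have no group sessions.
- **Sample size:** "a minimum of 20 subjects per group (10 % loss) will be required", from 80% power, alpha 0.05 and a Cohen's d of "0.87 in the QuickPIPER scale of CRF". No ICC or design effect appears, and the sidedness of the test is not given.
- **Statistical treatment:** on the between-arm comparison the text says "This is followed by inferential analysis by difference values between the outcome variables in both groups", with a p-value "<0.05 will be considered statistically significant". It names no test and mentions neither exercise group nor physiotherapist.

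**The concern.** This is a partially nested design: patients in the exercise arm share sessions and staff, and patients in the control arm do not. The primary outcome is self-reported fatigue. A shared instructor, shared encouragement and the dynamics of a small group could plausibly make outcomes within a group more alike. If they do, 20 exercise patients in about two groups carry less information than 20 independent patients.

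Two things are then at stake. The power is lower than the calculation implies. A comparison that ignores grouping also uses a standard error that is too small, so the p-value and confidence interval look better than they should. The Discussion expects quick uptake of the results in practice guidelines, so an interval that is too narrow would matter.

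**Working it through.** **Inputs from the article.** d = 0.87, alpha 0.05, power 80%, 20 per group with 10% loss (Sample size); groups of eight to ten, exercise arm only (Intervention).

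**Assumptions.** The 10% loss is already inside the 20, so 20 × 0.9 = 18 patients per arm are evaluable. They form two closed groups of m = 9. The total variance is the same in both arms. The ICC is not in the documents; 0.01 to 0.10 is shown.

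**Step 1: reproduce the 20 per group.** Two-sample t-test for independent patients, noncentral t:
- One-sided 0.05: 17 per arm gives 79.9% power and 18 gives 81.9%, so n = 18, and 18/0.9 = 20. This matches.
- Two-sided 0.05: 22 per arm are needed (80.5%), and 22/0.9 = 24.4, so 25. This does not match. With 18 per arm, two-sided power is 71.8%.

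The stated figure is therefore an independent-patient calculation with a design effect of 1.

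**Step 2: one-arm design effect.**
- Exercise arm: DE = 1 + (m − 1) × ICC = 1 + 8 × ICC.
- Variance inflation of the difference: VIF = (DE + 1)/2.
- Standard error in SD units: √((DE + 1)/18).
- Effective exercise patients: 18/DE.

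**Step 3: power and error.** Power is from the noncentral t with 34 df and noncentrality 0.87/SE, treating the ICC as known. Error is that of an ordinary two-sided t-test ignoring the groups, by simulation (at least 100,000 trials per setting).

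| ICC | DE | VIF | Effective n (exercise) | Two-sided error, unadjusted | Power, one-sided | Power, two-sided |
|---|---|---|---|---|---|---|
| 0 | 1.00 | 1.00 | 18.0 | 5.0% | 81.9% | 71.8% |
| 0.01 | 1.08 | 1.04 | 16.7 | 5.4% | 80.6% | 70.1% |
| 0.02 | 1.16 | 1.08 | 15.5 | 5.9% | 79.3% | 68.4% |
| 0.05 | 1.40 | 1.20 | 12.9 | 7.4% | 75.5% | 63.9% |
| 0.10 | 1.80 | 1.40 | 10.0 | 9.9% | 69.7% | 57.3% |

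Example at ICC 0.05: DE = 1 + 8 × 0.05 = 1.40; SE = √(2.40/18) = 0.365; noncentrality = 0.87/0.365 = 2.38.

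An approximate check on the error, with no simulation, is 2 × (1 − Φ(1.96/√VIF)). At VIF 1.20 this gives 7.4%. For a one-sided unadjusted test the simulated error is lower: about 5.3%, 6.8% and 8.4% at ICC 0.01, 0.05 and 0.10.

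**Step 4: what belongs to clustering.** Only the fall within each power column does. At ICC 0.05 that is 81.9 − 75.5 = 6.4 points one-sided, or 71.8 − 63.9 = 7.9 points two-sided. The gap between the stated 80% and 71.8% comes from the sidedness of the test and exists before any clustering.

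**Step 5: sensitivity to group size.** With no loss and two groups of 10, DE is 1.09, 1.45 and 1.90 at ICC 0.01, 0.05 and 0.10. The unadjusted two-sided error is about 5.5%, 7.7% and 10.5%.

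**The case against.** - **The ICC is unknown and may be low.** This stands. Nothing in the article shows that 0.05 or 0.10 applies, and setting loads and intensity for each patient may reduce it. It does not make it zero, because sessions and staff are still shared. A reader might infer that the stated power and 5% error rate simply fail. The documents do not support that: at ICC 0 both hold on the one-sided reading, and at 0.01 power is still above 80% and the excess error is under half a point.

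- **The analysis text names no test.** This stands. A reader might infer that the planned test treats all patients as independent, but that would be an inference from silence, and an analysis plan not shown could deal with grouping. The sample size is different: it is a completed calculation, and Step 1 shows what went into it.

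- **Two closed groups of nine is an assumption.** This stands. The Background section has training start on day 1 of each patient's chemotherapy, so membership may change over time. With open groups, m = 9 is only a rough guide and a patient may have no single group label.

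- **About two groups cannot support a cluster model.** Correct. With separate arm variances and 1 df for the exercise-group means, the Satterthwaite df is about 3.8, 2.9 and 2.4 at ICC 0, 0.05 and 0.10. The critical t is then 2.84, 3.28 and 3.71 instead of 2.03. A partially nested mixed model is therefore not a sensible request here. Restating power, or widening the interval at a fixed ICC, requires no variance estimate, so this objection does not reach those steps.

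**Conclusion.** The point holds in conditional form. The exercise arm is grouped and the control arm is not, the sample size allows for no correlation within groups, and the analysis text is silent on it. If outcomes correlate within exercise groups, power is below the independent-patient figure and an unadjusted comparison exceeds 5% error.

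The size depends on an ICC that the documents do not give: nothing at 0, little at 0.01, material from about 0.05. On the one-sided reading that reproduces the sample size, the margin over 80% is gone by ICC 0.02. The power figures treat the ICC as known and are therefore somewhat optimistic, since about two groups can hardly estimate it. They also rest on 18 evaluable per arm in closed groups of nine.

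Comparing the two-sided figures directly with the stated 80% would charge clustering with a shortfall that belongs to the unstated sidedness.

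**What to change.** 1. **Sample size:** restate the power for the planned numbers with the one-arm design effect over ICC 0.01 to 0.10, giving the group size assumed and the sidedness of the test.
2. **Data collection:** record each patient's exercise group, or the sessions attended, and the physiotherapist. State whether groups are closed or open. The article says recruitment had not opened at submission. This is easy to record prospectively and may be hard to recover later.
3. **Statistical treatment:** keep the main comparison. Beside it, as a sensitivity analysis, report the confidence interval and p-value with the exercise-arm variance inflated at fixed ICCs of 0.02, 0.05 and 0.10. Do not add a partially nested mixed model.

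**Cost.** A paragraph of wording and a small addition to the data form; no extra patients. The stated power becomes less favourable. With equal arms and the same critical value, the sensitivity interval is wider by √1.08, √1.20 and √1.40, that is about 4%, 10% and 18%. Its width is set by the assumed ICC, so it should be presented as a range and not as an estimate.

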### Measurements

During the study, course participants will complete questionnaires and interviews, and tests of physical condition and sampling of tissues and cells will also be carried out. The primary outcome will be the change in CRF as measured by the QuickPIPER questionnaire and also general health and quality of life will be evaluated by validated scales, as well as an objective assessment of physical condition by a standardized and validated dynamometer test.

### Primary outcomes

The primary outcome will be fatigue, assessed by the revised CRF QuickPIPER scale [21], with the semi-structured interview [11] to define CRF phenotype.

### Secondary outcomes

Secondary outcome variables were distributed among the questionnaires, a physical condition test and biological samples.

Medical and demographic information will be collected about age, marital status, educational level and surgery for GCC. State of physical and mental health will be evaluated through the short form (SF-12) [22] and quality of life (EuroQoL-5D and EuroQoL-VAS) questionnaires [23]. The study of fatigue will be completed by the assessment of mood state by POMS (Profile of Mood States). It is possible to obtain an overall index of altered mood and seven partial measures: stress/anxiety, depression/rejection, anger/hostility, vigor/activity, fatigue/inertia and confusion/bewilderment [24].

A physical condition test will be included to assess isotonic peak strength of knee extension (quadriceps), knee flexion (hamstring), elbow extension (triceps brachii) and elbow flexion (biceps brachii) by one dynamometric measurement instrumented with Powertruck II of JTECH, following the protocol described by Daniels and Worthingham [25]. Hand grip strength will be evaluated by the hydraulic dynamometer JAMAR [26].

Biological samples are taken to determine the immunohistochemical, molecular and systemic changes.

Metabolomic analysis and systemic inflammation will be measured in 10-ml venous blood samples following clinical standards. Metabolomics can be used to systematically measure the population of biomarkers (metabolites), creating profiles among healthy individuals versus those with specific diseases [27]. Moreover, metabolomics may provide signs of a metabolic problem or injury with high precision and less cost than genomics, transcriptomics or proteomics and can, therefore, be a very suitable technique for generalized scientific research [28, 29]. Fluid metabolomic analysis is being used successfully in cancer [30–33]). Circulating plasma cytokines will be analyzed using antifreeze, ethylenediaminetetraacetate (EDTA). Plasma will be stored at −80 °C until further analysis. C-reactive protein (CRP), tumor necrosis factor alpha (TNF-α), interleukin (IL)-6 IL-18, IL-4 and IL-10 will be determined by ELISA (Enzyme-linked Immunosorbent Assay) as previously described [34]. Total cholesterol, high-density lipoprotein (HDL), low-density lipoprotein (LDL) cholesterol, triglycerides, glucose and insulin will be determined by standard laboratory procedures.

### Sample size

Version 3.1 G-Power was used to estimate the sample size and a minimum of 20 subjects per group (10 % loss) will be required “a priori” to have sufficient statistical power (80 %), alpha error (0.05) and a clinical effect Cohen’s *d* = 0.87 in the QuickPIPER scale of CRF [24].

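### The 20 per group reproduces only as a one-sided calculation that the protocol never declares; at a two-sided 0.05 the power for d = 0.87 is about 72% to 76%, not 80%

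*Protocol article*

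**What the plan says.** The Sample size section gives every input to the calculation except the number of tails:

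- Software and size: "Version 3.1 G-Power was used to estimate the sample size and a minimum of 20 subjects per group".
- Allowance for loss: "a minimum of 20 subjects per group (10 % loss) will be required".
- Power and error rate: "sufficient statistical power (80" per cent) and "alpha error (0.05").
- Effect: a Cohen's d of "0.87 in the QuickPIPER scale of CRF [24"].

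The Statistical treatment section plans a between-group comparison of difference values, by intention to treat, and sets the significance rule as "A value of *p* <0.05 will be considered statistically significant". It does not mention one- or two-sided testing. Neither section declares or justifies a one-sided test.

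**The concern.** A significance rule of p < 0.05 with nothing further said is ordinarily read as two-sided. A reader who takes it that way and enters the stated inputs into a two-sample t-test does not get 20 per group.

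The number of tails is not a minor detail here. It moves the requirement from 20 to 25 randomised per group once 10% loss is allowed for. QuickPIPER fatigue is the primary outcome, so this is the trial's main design figure. The planned effect is already large on the protocol's own scale (0.8 or more), which leaves little margin if the true effect is smaller. The Discussion also expects the results to inform practice guidelines whichever way the hypothesis falls, so a null result would be read against the stated 80%.

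**Working it through.** **Inputs (Sample size section).** d = 0.87; alpha = 0.05; power = 80%; equal groups; 20 per group; 10% loss. Because d is standardised, no SD is needed. It is taken here in SD units of whatever variable is compared between groups.

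**Method.** Two independent means, noncentral t, which is the calculation G*Power makes. With n evaluable per group:

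- noncentrality δ = d × √(n/2), degrees of freedom 2n − 2
- one-sided power = P(T′ > t at 0.95)
- two-sided power = P(|T′| > t at 0.975)
- randomised number = evaluable number / (1 − 0.10), rounded up

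**Step 1: reproduce the stated 20.** One-sided 0.05:

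- n = 17: δ = 0.87 × √8.5 = 2.537, critical t (32 df) = 1.694, power 79.9%, just short.
- n = 18: δ = 0.87 × √9 = 2.610, critical t (34 df) = 1.691, power 81.9%.
- The exact solution is n = 17.06, so 18 evaluable, and 18/0.9 = 20. This matches the protocol exactly.

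**Step 2: the same inputs, two-sided 0.05.**

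| Evaluable per group | δ | Critical t (df) | Power |
|---|---|---|---|
| 18 (20 less 10%) | 2.610 | 2.032 (34) | 71.8% |
| 20 (no loss) | 2.751 | 2.024 (38) | 76.5% |
| 22 | 2.886 | 2.018 (42) | 80.5% |

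The exact solution is n = 21.74, so 22 evaluable; 22/0.9 = 24.4, so 25 randomised per group. This is not 20.

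**Step 3: detectable effect at 80% power, two-sided.** d = 0.96 with 18 evaluable per group and d = 0.91 with 20.

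**Step 4: does another two-sided route lead to 20?**

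- Normal approximation: 21 evaluable, and 21/0.9 = 23.3, so 24 randomised. Power is 74.2% at 18 and 78.6% at 20.
- Mann-Whitney, dividing 21.74 by a relative efficiency of 0.955 or 0.864: 22.8 or 25.2 evaluable per group, before any loss.

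No two-sided variant tried gives 20, whether 20 is read as randomised or as evaluable.

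**The case against.** The strongest reply is that no stated input contradicts the 20. The protocol gives alpha without the number of tails, and one admissible choice reproduces the figure exactly. The aim is worded directionally, as improving fatigue, so a one-sided plan would conflict with nothing in the text. This is also a journal article, and the full protocol or analysis plan may name the test. This much stands: the calculation is not shown to be wrong, and the one-sided origin is an inference from the match.

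It does not dispose of the point. A directional aim does not declare a one-sided test. The article chose to print a power claim, and that claim depends on an assumption that it does not print and that most readers would fill in the other way.

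A second reply is that 72% is the less favourable case: 20 is described as a minimum, and analysis is by intention to treat. If all 20 have outcome data, two-sided power is 76.5%, so both figures belong in the restatement. But the wording "20 subjects per group (10 % loss") reads as including the loss, and intention to treat does not by itself supply missing outcomes. Even with no loss the two-sided figure is 3.5 points short.

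A third reply is that baseline adjustment might recover the power. The article names no such model for this comparison, gives no baseline correlation, and does not say whether d is scaled to the final score or to the change. Nothing in it supports counting on such a gain.

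**Conclusion.** The point holds as a conditional one. The stated 20 per group delivers 80% power for d = 0.87 only if the test is one-sided at 0.05, and the protocol does not say that it is. If the test is two-sided at 0.05, power is about 72% with 18 evaluable per group and about 76% with 20, and 80% would need 22 evaluable per group.

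A reader might go further and infer that the trial lacks its stated power outright, so that a true effect of the planned size would be missed about 28% of the time instead of 20%. The document does not support that without the two-sided condition: under a one-sided 0.05 test the power is 81.9% at 18 per group. Even under a two-sided test, 28% is the figure for 18 evaluable; with all 20 it is 100 − 76.5 = 23.5%.

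The figures assume a two-sample t-test, equal groups, and d in SD units of the analysed variable. Severity: should fix, as a clarification and restatement.

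**What to change.** In Sample size and in Statistical treatment, state that the primary comparison is two-sided at 0.05. Restate the power along these lines: with 20 randomised per group, a two-sided 5% t-test has about 72% power for d = 0.87 if 18 per group are evaluable and about 76% if all 20 are, with d in SD units of the analysed variable; the effect detectable with 80% power is d = 0.96 or 0.91 respectively.

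If a one-sided test was intended, say so and justify it in both sections; the 20 per group then stands as calculated.

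The cost is a sentence or two and a less favourable stated power. The restatement needs no extra patients. If the sponsor prefers to keep 80% power with a two-sided test, the stated inputs require 22 evaluable, or 25 randomised, per group; that is a design choice beyond this correction.
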